**Methods/Design:**

The 24 month mixed methods cohort evaluation of 600 prevalent centre based HD patients is nested within a 30 month quality improvement program that aims to scale up SHC at 12 dialysis centres across England. SHC describes an intervention where patients who receive centre-based haemodialysis are given the opportunity to learn, engage with and undertake tasks associated with their treatment.

Following a 6-month set up period, a phased implementation programme is initiated across 12 dialysis units using a randomised stepped wedge design with 6 centres participating in each of 2 steps, each lasting 6 months. The intervention utilises quality improvement methodologies involving rapid tests of change to determine the most appropriate mechanisms for implementation in the context of a learning collaborative. Running parallel with the stepped wedge intervention is a mixed methods cohort evaluation that employs patient questionnaires and interviews, and will link with routinely collected data at the end of the study period. The primary outcome measure is the number of patients performing at least 5 dialysis-related tasks collected using 3 monthly questionnaires. Secondary outcomes measures include: the number of people choosing to perform home haemodialysis or dialyse independently in-centre by the end of the study period; end-user recommendation; home dialysis establishment delay; staff impact and confidence; hospitalisation; infection and health economics.

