### Study design and timeline

End points will be quantified following a stepped-wedge introduction of the intervention, in which 6 centres are randomly allocated to start implementation in step 1, with the remaining 6 starting in step 2. Each step lasts 6 months, and including the baseline phase the study lasts 24 months. The study phases are outlined in Fig. 1 and the schedule of instruments in Table 1. The programme entered the baseline phase in October 2016.

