### Outcome measures and quantitative data collection

Efficacy Endpoints - The primary binary outcome is a change in the proportion of sampled HD patients completing 5 or more out of 14 tasks (Table 2). The secondary binary outcome is an absolute increase HHD and in centre independent dialysis of 4% within participating centres.

Quality and Safety Endpoints - Changes in patient activation [14]; quality of life (EQ-5D-5L) [15]; POS-S Renal symptom score [16] will be assessed using the “Your Health Survey” developed as part of the NHS England supported Transforming Participation in Chronic Kidney Disease program [17]. Responses to this survey will be transferred to the UK Renal Registry and uploaded to PatientView [18] for participating patients to review themselves and to be used to inform clinical consultations. Hospitalisation (all-cause and cause specific) will inform cost, benefits and harms assessments. The economic evaluation will take an NHS and social care perspective and will compare SHC with usual care in a cost-utility analysis based on a cost-per quality adjusted life years (QALYs) approach. The EQ-5D-5L will be used to measure health related quality of life at baseline, six and 12 months. Resource use will be estimated from a range of sources including an adapted cost questionnaire [19] and non-participant observation to quantify time spent performing HD tasks by patients and staff.

Hospital Episode Summary data will be used for information on comorbidity at the time of recruitment (by reviewing diagnosis codes from admissions up to 5 years prior to the start of the SHAREHD programme), hospitalisation (all cause and cause specific) before and after the implementation of SHAREHD to assess for benefits and harms, and inform health economic analyses. Similar datasets and diagnostic codes have been used to identify harms from hospital and home-based haemodialysis therapies and assess cost [20].

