### Statistical analysis plan

The primary and secondary outcomes will be compared across the intervention and control clusters using a longitudinal random (or multi-level mixed) effects logistic regression model (with time, phase or step), group (intervention or control) and individual patient characteristics such as age and gender as covariates; and the renal unit or cluster as a random effect. These models will take into account the clustering of outcomes by units. The odds ratio estimate for the intervention effect and its associated confidence interval will be reported from the model. Statistical associations between patient characteristics, dialysis schedules and outcomes will also be explored.

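### Hospitalisation is described as a before/after comparison that is not reconciled with the stepped-wedge analysis, and the only model stated does not suit admissions

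*Protocol article*

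**What the plan says.** Four places in the protocol article bear on this.

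- *Outcome measures and quantitative data collection*, last paragraph: hospital episode data will supply "hospitalisation (all cause and cause specific) before and after the implementation of SHAREHD to assess for benefits and harms". No comparator, model or period adjustment is named in that sentence.
- The same section places hospitalisation under the quality and safety endpoints: "Hospitalisation (all-cause and cause specific) will inform cost, benefits and harms assessments". The only secondary outcome named as such there is a different one: "The secondary binary outcome is an absolute increase HHD and in centre independent dialysis of 4% within participating centres".
- *Abstract, Methods/Design*: the list of secondary outcome measures includes "home dialysis establishment delay; staff impact and confidence; hospitalisation; infection and health economics".
- *Statistical analysis plan*: "The primary and secondary outcomes will be compared across the intervention and control clusters", by a longitudinal mixed-effects logistic model ("with time, phase or step), group (intervention or control" among the covariates), with the renal unit as a random effect and an odds ratio as the reported result.

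On timing, *Study design and timeline* gives 6-month steps and 24 months in all, and says "The programme entered the baseline phase in October 2016".

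**The concern.** Hospitalisation is the outcome that the article ties explicitly to judging benefits and harms, and it also feeds the economic evaluation. The Methods attach one comparison to it by name, before against after implementation. The controlled comparison reaches it only through the abstract's classification.

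Each reading has a problem:

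- **Literal before/after.** Implementation always comes later in calendar time than no implementation, so the contrast absorbs any secular trend, any seasonal imbalance and the decline of an ageing prevalent dialysis cohort. These can look like harm, or conceal it.
- **Analysis section governs.** The comparison is then controlled and time-adjusted, but the stated model is for a yes/no outcome. Admissions recur, and patients are observed for unequal times because some die or are transplanted.

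An analyst following the article could defend either approach, and the two could give different answers on harm.

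**Working it through.** The article gives no effect size, rate or power for hospitalisation, so there is no planned figure to reproduce. The check has three parts.

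**1. Bias of a before/after contrast under a pure time trend.** Inputs: 12 centres, 6 crossing over at each of 2 steps, and 3 periods including baseline (*Sample size calculation*). Assumption: the outcome rises by d per 6-month period in every centre, with zero intervention effect. Number the periods 0, 1, 2.

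| Centres | Mean period before | Mean period after | Difference |
|---|---|---|---|
| Step 1 | 0 | (1 + 2)/2 = 1.5 | 1.5d |
| Step 2 | (0 + 1)/2 = 0.5 | 2 | 1.5d |

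- Within-centre before/after: bias 1.5d. For d = 1, 2 or 5 percentage points, that is 1.5, 3.0 or 7.5 points.
- Pooled over equal-sized cells: before = (0 + 0 + 1)/3 = 1/3 and after = (1 + 2 + 2)/3 = 5/3, so the bias is 1.33d.
- Period-adjusted: in period 1 both groups have moved by d since baseline, so (d − 0) − (d − 0) = 0. A least-squares fit with period terms on the 12 × 3 layout also gave zero.
- If the 24 months are treated as four 6-month periods, step-1 centres give (1 + 2 + 3)/3 − 0 = 2 and step-2 centres give (2 + 3)/2 − (0 + 1)/2 = 2, so the within-centre bias becomes 2d.

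The size of d is not in the article. These results show how a trend carries through, not how large the trend is.

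**2. How unequal time at risk becomes.** Input: 17% annual mortality (*Sample size calculation*) and 600 recruits. Proportion alive at t years = 0.83^t.

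| Months | Alive | Of 600 |
|---|---|---|
| 6 | 91.1% | 547 |
| 12 | 83.0% | 498 |
| 18 | 75.6% | 454 |
| 24 | 68.9% | 413 |

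This is before transplants. About three in ten participants would not complete 24 months at risk.

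**3. What the logistic model does with such data.** To fit it, admissions must be reduced to any or none per period. One admission and four then count alike, and a patient who dies a month into a period without an admission counts the same as one followed throughout. Neither frequency nor exposure enters the odds ratio.

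**The case against.** The strongest reply is that the before/after sentence describes what will be extracted from a data source, not an analysis. Every centre in a stepped wedge has time before and after implementation, so admissions from both are what a controlled model needs. The abstract makes hospitalisation secondary, the analysis section compares secondary outcomes across clusters with time terms, and the economic evaluation is described as comparing the programme with usual care. A condensed article may also leave the model for a non-primary outcome to an analysis plan that is not shown, and any admission in a period is a legitimate binary outcome.

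Much of this stands. A reader might infer that harms will be judged by an uncontrolled comparison, but the documents do not say so. The lack of a detailed hospitalisation model is not a fault in itself. What remains is that the sentence names a contrast and its purpose, that the Methods class the endpoint apart from the secondary outcome, and that the one model stated for secondary outcomes is logistic.

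Two further inferences are tempting and should not be drawn.

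- **A general survivorship bias of 1.05 to 1.14.** Six-month mortality is 1 − 0.83^0.5 = 0.089. If those who die do so mid-window and are admitted at k times the usual rate, the spurious rate ratio is (0.911 × 6 + 0.089 × 3k)/(0.911 × 6 + 0.089 × 3) = 1.05, 1.09 and 1.14 for k = 2, 3 and 4. This requires a before window lying wholly ahead of recruitment, and the range for k is an assumption. Recruitment takes place during baseline, so patients can die after consent and before implementation. Step-2 centres also have the whole of step 1 as before time.
- **Seasonal bias in every centre.** If baseline lasted 6 months from October 2016, step-1 centres would set October to March against a first after period of April to September. Step-2 centres would then have October to September on both sides over 24 months, which is balanced. The baseline length is itself inferred, because two 6-month steps leave 24 − 12 = 12 months to allocate and the timeline figure is not shown.

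**Conclusion.** The point holds as an unreconciled description with an unsuitable stated model. The outcomes section, the abstract and the analysis section do not together say how hospitalisation will be compared. A literal before/after contrast carries a time trend into the effect estimate at 1.5d in the three-period layout (2d with four periods), and period adjustment removes it. The alternative reading is controlled but discards repeat admissions and person-time in a cohort losing 17% a year to death alone.

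The direction and size of any actual bias in admissions cannot be given from the article, since trend and season are not quantified. The bias result assumes a linear trend common to all centres, and the survival figures assume constant mortality. The primary outcome and its sample size are unaffected.

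**What to change.** In both *Outcome measures and quantitative data collection* and *Statistical analysis plan*, state that all-cause and cause-specific hospitalisation is analysed within the stepped-wedge structure, and replace the before/after wording as the comparison. Specify:

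- a negative binomial or Poisson mixed model for admissions per patient-period, with log person-time at risk as offset;
- categorical calendar period and current intervention status as fixed effects, and centre and patient random effects;
- follow-up for this analysis ending at death or transplant, with deaths reported by condition alongside.

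Limit the logistic model to binary outcomes, and class hospitalisation the same way in the abstract and the Methods.

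The cost is wording only, provided the linked records carry admission dates, as such data should. The downside is wider intervals than a simple before/after contrast, because concurrent randomised control exists for only one 6-month step of the 24 months.

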### Qualitative investigation and realist evaluation

Realist evaluation will be conducted complementary to the quantitative primary and secondary endpoints to determine if and how SHC works, for whom and in what context. Building on existing theories gained from literature, key stakeholders and the Yorkshire SHC pilot, a logic model will be constructed. This model will be developed throughout the project, and used to refine and test specific relevant hypotheses. Key contextual service characteristics will be determined across the units to further understand the linkage between variability in context, implementation and outcomes, and to inform interview sampling strategies. Semi-structured interviews will be conducted before and after the intervention with approximately 24 patients and 24 members of staff across participating sites. Programme theory and expert opinion will inform a stakeholder map from which key individuals will be selected for interview.

### Sample size calculation

Assuming that the baseline level of completing 5 tasks is around 15%, an ICC of 0.05 and an average cluster size of 25 HD patients; then using the STATA stepped wedge command [21] with a stepped wedge design of 3 steps (including baseline) and 12 clusters, with 6 clusters randomised at each step, we will have 90% power to detect an increase in the event rate from 15% to 30% as statistically significant at the 5% two-sided level. If we assume that the baseline level of the secondary outcome measure of HHD is around 2% in participating clusters an ICC of 0.05 and an average cluster size of 25 HD patients; then with a stepped wedge design of 3 steps (including baseline) and 12 clusters, with 6 clusters randomised at each step will we have 80% power to detect an increase in the event rate from 2% to 7.2% as statistically significant at the 5% two-sided level. In recognition of a mortality rate of 17% per annum [20], a background renal transplantation rate and to mitigate the risk of incomplete data collection, the target recruitment per participating site was increased to 50.

### Data collection

Paper questionnaires will be batched, and securely transferred to the Sponsor site (Sheffield Teaching Hospitals NHS Foundation Trust)^1^ to be entered into the research database and will be retained securely for audit purposes. Interview audio recordings will encrypted, pseudo-anonymised and be destroyed after transcription.

### Statistical analysis plan

The primary and secondary outcomes will be compared across the intervention and control clusters using a longitudinal random (or multi-level mixed) effects logistic regression model (with time, phase or step), group (intervention or control) and individual patient characteristics such as age and gender as covariates; and the renal unit or cluster as a random effect. These models will take into account the clustering of outcomes by units. The odds ratio estimate for the intervention effect and its associated confidence interval will be reported from the model. Statistical associations between patient characteristics, dialysis schedules and outcomes will also be explored.

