### Intervention

The intervention at the centre of this study is that centre based HD patients are given the choice to undertake treatment related tasks, listed in Table 2. These range from performing observations, preparatory hygiene, setting up the dialysis machine, securing dialysis access, programming the machine, initiating monitoring and discontinuing/completing dialysis.

**Table 2 Tab2:** Shared Haemodialysis Care treatment tasks (note some tasks are mutually exclusive)

Patient preparation	Machine Preparation & Dialysis Initiation	During and after dialysis
Measuring your weight	Lining your dialysis machine	Responding to your machine alarms
Measuring your blood pressure and pulse	Priming your dialysis machine	Disconnecting the lines and completing your dialysis
Measuring your temperature	Preparing your dressing pack	Applying pressure to your needle sites OR Locking your own tunnelled line
Washing your hands prior	Programming your dialysis machine	Giving your own anaemia injections (such as epoetin)
	Needling your fistula/graft OR Preparing your tunnelled line	
	Connecting the lines to your fistula/graft/tunnelled line and commencing dialysis	

A series of learning events are planned with teams comprising approximately five individuals from each participating site. These include clinicians, nursing staff, patient partners and additional relevant personnel (e.g. psychologist, service managers as determined by individual sites). The learning events are designed to review the objectives of SHC, share patient and clinician experience, teach and review quality improvement methodologies, and develop rapid tests of change to optimise local implementation. Learning is underpinned through the SHC website [12], teleconferences, social media platforms and newsletters, while staff education is supported by a bespoke nursing training course developed during pilot work [13]. A patient advisory group has been established in order to support their involvement and ensure that the programme maintains patient focussed objectives.

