The strengths of our protocol include the stepped wedge design with a random allocation to reduce the risk of bias, particularly relevant in a quality improvement intervention. We selected instruments on the basis of clear evidence of their utility. The Patient Activation Measure (PAM) [24] is being used under licence from NHS England to explore factors that impact on readiness to participate in dialysis related tasks. Low patient activation is associated with a range of poorer healthcare outcomes including readmission to hospital, medical errors and loss of confidence in healthcare providers [25]. The questions on mobility, symptom burden, cognition, health literacy and attitudes to self-needing included in our questionnaires (Table 1) were identified though our pilot work as potentially impacting on the individual’s ability to participate in HD tasks. Identifying barriers to involvement is clearly important particularly as the SHC concept is that patients are supported to take on as much or as little as they feel able to do. A small amount of engagement is meaningfully different from an environment where participation is discouraged. The duration of the study is sufficient to assess whether perceived benefits to patients are sustained or whether the repetitive nature of dialysis treatment results in a loss of enthusiasm for engagement over time. Patient partners are central in the design of the intervention, selection of endpoints and instruments and ensuring outputs remain relevant to the end-user (co-production).

The challenges of the adopted approach include competing pressures that health care professionals face in their day to day work and that the heterogeneity of HD units may limit the effectiveness of the intervention. To address these concerns we have adopted quality improvement methodologies that are intentionally tailored to support local configuration. Participant drop-out during the course of the 24 month protocol has been mitigated by doubling the initial cohort size above that required by the power calculation.

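### One constant intervention term in a two-sequence stepped wedge weights the longest exposure negatively, so an effect that builds or fades with a centre's time since start gives a misleading primary odds ratio

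*Protocol article*

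**What the plan says.** The protocol article's Statistical analysis plan section sets out a mixed logistic model with time (or phase or step), a random effect for the renal unit, and "group (intervention or control) and individual patient characteristics such as age and gender as covariates". One odds ratio for the intervention, with its confidence interval, is to be reported. Nothing in the article lets the effect differ by how long a centre has been exposed.

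Study design and timeline has two sequences: "6 centres are randomly allocated to start implementation in step 1, with the remaining 6 starting in step 2". On duration it says: "Each step lasts 6 months, and including the baseline phase the study lasts 24 months". The Sample size calculation uses a "stepped wedge design of 3 steps (including baseline) and 12 clusters, with 6 clusters randomised at each step".

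Two other places suggest that the effect may not be constant. Under Intervention, the learning events serve to "develop rapid tests of change to optimise local implementation". The Discussion says the study is long enough to assess "whether perceived benefits to patients are sustained or whether the repetitive nature of dialysis treatment results in a loss of enthusiasm".

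**The concern.** In the last step of the three-phase design every centre is coded as intervention. Step-1 centres are then in months 6-12 of exposure and step-2 centres in months 0-6. A single term treats these as the same effect. Any true difference between them looks to the model like a difference between centres, and the correction for that moves the estimate the wrong way. Growth in the effect is subtracted, and fading is added.

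The primary conclusion is at stake. An intervention that needs some months to take hold, and then reaches the planned 15-point gain, could show an odds ratio close to 1. One that works briefly and fades could look better than it ever was.

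**Working it through.** **Inputs from the Sample size calculation:** "baseline level of completing 5 tasks is around 15%, an ICC of 0.05 and an average cluster size of 25 HD patients"; "90% power to detect an increase in the event rate from 15% to 30% as statistically significant at the 5% two-sided level"; six centres per sequence; three phases. I take the cluster size as 25 per centre per phase, which is the reading that reproduces the stated power. Sequences are 0-1-1 and 0-0-1.

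**1. The plan's own figure.** In units of the total variance 0.15 × 0.85 = 0.1275, a centre-phase mean has within-centre part a = (1 - 0.05)/25 = 0.038 and centre part b = 0.05. The Hussey-Hughes variance of the constant effect is

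(2/6) × 0.1275 × a(a + 3b)/(a + 2b) = 0.0425 × 0.038 × 0.188/0.138 = 0.00220, so SE = 0.0469.

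Power for 15 points is Φ(0.15/0.0469 - 1.96) = 89.2%, against 90% stated. The same method gives 80.7% for the secondary outcome, against 80% stated. So the stated power also rests on a constant effect.

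**2. What the single term estimates.** Let d1 and d2 be the true effects in months 0-6 and 6-12. With categorical phase, only the differences between the two sequences are informative. By phase their expectations are (0, d1, d2 - d1). The constant-effect model expects (0, d, 0). Generalised least squares with a random centre intercept gives

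estimate = (d1 - c·d2)/(1 - c), with c = b/(a + 3b).

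- Weight on d1: (a + 3b)/(a + 2b) = 0.188/0.138 = 1.362
- Weight on d2: -b/(a + 2b) = -0.050/0.138 = -0.362

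**3. Sensitivity of the weight on d2 (three phases).**
- ICC 0.01: -0.168
- 50 per centre and phase: -0.420
- Within-patient correlation 0.5 (an assumption; the article gives none): -0.439
- ICC near 0: the negative weight vanishes

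**4. Reading of the 24 months.** Two 6-month steps plus a 6-month baseline make 18 months, and the phase figure is not shown. There are two ways to place the other 6 months:
- Second 6-month baseline period: weights 0.238/0.188 = 1.266 on months 0-6 and -0.050/0.188 = -0.266 on months 6-12.
- Fourth, all-intervention phase kept in the model: 1.266, 0 and -0.266 on months 0-6, 6-12 and 12-18. With linear instead of categorical time, these become 1.376, 0.092 and -0.468.

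**5. Size, three phases, in percentage points.**

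| True effect, months 0-6 | months 6-12 | Single-term estimate |
|---|---|---|
| 15 | 15 | 15.0 |
| 7.5 | 15 | 1.362 × 7.5 - 0.362 × 15 = 4.8 |
| 5 | 15 | 1.362 × 5 - 0.362 × 15 = 1.4 |
| 15 | 5 | 1.362 × 15 - 0.362 × 5 = 18.6 |

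Power to declare a benefit is about 17% in the second row and 5% in the third. With four phases, effects of 5, 10 and 15 give 1.266 × 5 - 0.266 × 15 = 2.3.

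**6. Odds-ratio scale.** A random-intercept logistic model was fitted to 6,000 simulated centres, three phases. True odds ratios of 1.42 then 2.43 (15% rising to 20%, then 30%) gave 1.19. Ratios of 2.43 then 1.42 gave 2.96. A constant 2.43 gave 2.46, so the logistic link is not the cause.

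**7. Calendar-time change.** Suppose every exposed centre has an effect of 5 points in phase 2 and 15 in phase 3. The sequence differences are (0, 5, 0) and the estimate is exactly 5, the phase-2 effect. No negative weight arises.

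**8. Precision with separate exposure terms (three phases, 25 per centre and phase).** SEs are 0.0503 for months 0-6, 0.0831 for months 6-12 and 0.0639 for their average, against 0.0469 for the constant term.

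**The case against.** Several points against the concern have force.

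- **Which exposure is affected.** A reader might infer that months 6-12 always carry the negative weight and that the estimate always falls outside the range of the true effects. The documents do not support that. With a fourth all-intervention phase, months 6-12 have weight 0. Effects of 10, 15 and 10 points then give 1.266 × 10 - 0.266 × 10 = 10.0, inside the range. A steadily building or fading effect is still estimated outside it.
- **Which clock.** The Discussion describes sites sharing what they learn, so step-2 centres may start from where step-1 centres have got to. If the effect grows only with calendar time, the single term is not distorted. The article does not say which pattern to expect, and the trajectories above are illustrations.
- **What the Discussion promises.** It says the study's duration allows sustained benefit to be assessed. It does not say that the primary odds ratio will do so, and the article has 3-monthly task data and a realist evaluation as well. So this is no contradiction. The passage shows only that the authors think change over time is possible.
- **Unseen analysis plan.** Supporting models may be set out in a full plan that is not shown. That would not remove the point, because the article itself fixes the single term and the single reported odds ratio.
- **Replacing the primary.** Making the months 0-6 effect the only primary result would change the estimand and leave out later benefit. At an SE of 0.0503 its power is about 17% for 5 points and 32% for 7.5. This objection stands, and the fix below does not ask for it.

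**Conclusion.** The concern holds conditionally. If the effect depends on a centre's own time since start, the planned term gives the longest exposure a negative weight: about -0.36 in the three-phase design at the planning values, or -0.27 with a fourth phase or a second baseline period. A steady build-up is then underestimated, to near null in plausible cases, and a steady decline is exaggerated. The exact weights are for a linear model with a random centre intercept; the logistic simulation shows the same direction and similar size. There is no distortion if the effect is constant or changes only with calendar time, and little if the ICC is close to 0. The documents do not show that the effect will build or fade. They give good reason not to rest the primary result on the assumption that it cannot.

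**What to change.** - Code phase as categorical, and state how many phases enter the model.
- Beside the constant-effect odds ratio, pre-specify a model that replaces the single term with indicators for time since the centre started: 0-6 months, 6-12 months, and any later period analysed.
- Report each term. State in advance that the constant-effect odds ratio will not be interpreted as the intervention effect if the terms differ materially.
- If the sponsor prefers an exposure-time term as primary, name it and restate the power.

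The exposure-time model uses data already planned, and as a supporting analysis it costs only precision. In the three-phase design the SE for months 0-6 is about 7-14% larger than that of the constant-effect estimate: 7% at 25 per centre and phase, up to 14% at 40 with an assumed within-patient correlation of 0.7. The SE for months 6-12 is about 1.8-2.0 times as large.

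Making such a term primary is more than a wording change. For a 15-point effect, the months 0-6 term has power Φ(0.15/0.0503 - 1.96), about 85%. The average of the two terms has 65% at 25 per centre and phase and 88% at 50. The constant term has 89% at 25, but only if the effect really is constant. The exposure-time model also needs the months 0-6 effect to be the same in both sequences, so it does not separate exposure time from calendar time.
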